# Effectiveness of a home-based re-injury prevention program on motor control, return to sport and recurrence rates after anterior cruciate ligament reconstruction: study protocol for a multicenter, single-blind, randomized controlled trial (PReP)

**DOI:** 10.1186/s13063-019-3610-2

**Published:** 2019-08-13

**Keywords:** Return to sports, Return to play, RTS, Recurrence, Re-injury, ACL, Motor control, Secondary prevention, Therapy, Rehabilitation, Post treatment, Functional outcome

## Abstract

**Background:**

Although anterior cruciate ligament (ACL) tear-prevention programs may be effective in the (secondary) prevention of a subsequent ACL injury, little is known, yet, on their effectiveness and feasibility. This study assesses the effects and implementation capacity of a secondary preventive motor-control training (the Stop-X program) after ACL reconstruction.

**Methods and design:**

A multicenter, single-blind, randomized controlled, prospective, superiority, two-arm design is adopted. Subsequent patients (18–35 years) with primary arthroscopic unilateral ACL reconstruction with autologous hamstring graft are enrolled. Postoperative guideline rehabilitation plus Classic follow-up treatment and guideline rehabilitation plus the Stop-X intervention will be compared. The onset of the Stop-X program as part of the postoperative follow-up treatment is individualized and function based. The participants must be released for the training components. The endpoint is the unrestricted return to sport (RTS) decision. Before (where applicable) reconstruction and after the clearance for the intervention (aimed at 4–8 months post surgery) until the unrestricted RTS decision (but at least until 12 months post surgery), all outcomes will be assessed once a month. Each participant is consequently measured at least five times to a maximum of 12 times. Twelve, 18 and 24 months after the surgery, follow-up-measurements and recurrence monitoring will follow. The primary outcome assessement (normalized knee-separation distance at the Drop Jump Screening Test (DJST)) is followed by the functional secondary outcomes assessements. The latter consist of quality assessments during simple (combined) balance side, balance front and single-leg hops for distance. All hop/jump tests are self-administered and filmed from the frontal view (3-m distance). All videos are transferred using safe big content transfer and subsequently (and blinded) expertly video-rated. Secondary outcomes are questionnaires on patient-reported knee function, kinesiophobia, RTS after ACL injury and training/therapy volume (frequency – intensity – type and time). All questionnaires are completed online using the participants’ pseudonym only.

Group allocation is executed randomly. The training intervention (Stop-X arm) consists of self-administered home-based exercises. The exercises are step-wise graduated and follow wound healing and functional restoration criteria. The training frequency for both arms is scheduled to be three times per week, each time for a 30 min duration. The program follows current (secondary) prevention guidelines.

Repeated measurements gain-score analyses using analyses of (co-)variance are performed for all outcomes.

**Trial registration:**

German Clinical Trials Register, identification number DRKS00015313. Registered on 1 October 2018.

## Background

The risk of suffering from a subsequent anterior cruciate ligament (ACL) injury following ACL reconstruction is increased 10-fold in comparison to the first-incidence risk. A recurrence risk of 10–25% is specified in the current literature [1, 2]. Such re-injuries often occur in the first years following the surgery [2], in particular during, or shortly after, the successful return to sport (RTS). It is a major goal of the RTS process to lead an athlete back to training and competition without exhibiting an excessively high risk for a subsequent rupture [3]. Important criteria to be fulfilled, beyond psychosocial readiness and (of course) morphological graft healing, are, particularly, the restoration of neuromuscular and motor function. More precisely, a combination of dynamic strength and jump landing tests have been shown as being predictive for a second ACL injury [4, 5]. Enhancing and, thus, restoring these functional abilities may consequently lead to a decrease in the re-injury risk [6]. Beyond these quantitative measures, the quality of dynamic jumping and cutting maneuvers, in particular the avoidance of a dynamic valgus position, are crucial for a positive RTS decision based on functional criteria [7, 8]. Qualitative assessments are used only infrequently [7, 8]. Furthermore, their responsiveness to functional changes as well as predictive value for a subsequent ACL injury remains mostly unknown. A current systematic review with meta-analyses on biomechanics during single-leg landings concludes that both movement quality and performance of functional tasks should be examined as RTS tests [9]. Irrespective of the evaluation goal or if they having been validated or not, RTS tests are commonly performed at one single assessment at the hypothetical end of the RTS process [10]. Performing a series of measurements with the purpose of monitoring changes over time during the RTS process may be more promising [10].

As strength and dynamic motor-control capacities, in particular, are preventive for a re-injury [4, 5], they have to be targeted in recurrence prevention programs. Inadequate knee mechanics also result from trunk displacement and unequal limb loading [11]; thus, it is not sufficient to only target the knee joint. As an important surrogate of functional restoration of the knee and, likewise, not only triggered by the knee joint solely, avoiding a dynamic knee valgus may be crucial to prevent subsequent injury [11, 12]. Although contextual overlap between therapeutic and preventive programs (such as the described dynamic motor-control enhancement and avoidance of a dynamic knee valgus) exists, the therapeutic focus after ACL reconstruction should shift from therapy to recurrence prevention after a certain rehabilitation time. Several prevention programs exist and have been validated in terms of preventive effects on a primary ACL rupture incidence [13]. Although theoretical evidence exists that such programs may be effective in the prevention of a subsequent ACL injury [6], their effectiveness for primary and, in particular, for secondary prophylaxis after successful ACL reconstruction, is still a matter of debate. Likewise, the implementation capacity of such programs into everyday training after the prescribed rehabilitation is unknown.

The aim of the study is to assess the effects and implementation capacity of a preventive approach (Stop-X program [14]) after ACL reconstruction. Effects on re-injury-related motor-control/function, re-injury rates and time to successful RTS form the focus of this study.

The null hypothesis is as follows: the Stop-X program, as part of the evidence-based care and rehabilitation after ACL rupture and reconstruction, is not systematically superior to standard rehabilitation in terms of its effects on neuromuscular function, re-injury rate risk and time until RTS success.

## Methods and design

### Study design**,** ethics and informed consent

A multicenter, single-blind, randomized controlled, superiority, two-arm trial will be adopted. The comparator arms are guideline rehabilitation plus Classic follow-up treatment versus guideline rehabilitation plus the Stop-X intervention.

Central ethical approval has been confirmed from the independent Ethics Committee of the Hessen Regional Medical Council (ref approval no. FF 104/2017) and we will not begin recruiting at other centers in the trial until local ethical approval has been obtained. The date of the central approval was 27 June 2018. The study was planned and is performed in agreement with the Declaration of Helsinki (Version Fortaleza 2013). The trial was registered in the German Clinical Trials Register (DRKS), registration number DRKS00015313 (DRKS, drks.de; 01. October 2018). All adverse events will be reported. Each participant signs an informed consent prior to study enrollment.

The primary outcome is the normalized knee-separation distance (%) during a standardized Drop Jump Screening Test (DJST).

### Participants

#### Sample size determination

No study to retrieve the minimal clinical relevant change for the primary outcome DJST has been published. For the sample size calculation (G*Power version 3.1), we thus considered the values from an interventional randomized controlled trial (RCT) [12]. The mean post-intervention value was 66.4% (standard deviation (SD) = 14.2%). Considering a target effect of Cohen’s *d* = 0.3 (= mean change of 0.3 × SD), a two-sided alpha-error level of 5% and beta-error level of = 50%; data from *N* = 174 (*n* = 87 per group) participants have to be analyzed to statistically find a between-group difference using gain-score analyses. Assuming a dropout-rate of 30%, a total of 250 (*n* = 125 per group) patients will be included.

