## Discussion

The primary aim of the study is to test the feasibility and effectiveness of an ACL secondary preventive intervention. To do so, a standardized diagnostic assessment and a randomized controlled, single-blind intervention design are used. The intervention consists of exercises to target deficits in motor control and dynamic knee axis steadiness. A strength of this intervention is its practicability. Furthermore, all exercises can be performed without (or only with a little) additional material.

Recurrence prevention and the according diagnostics during and after RTS following ACL reconstruction are, except in professional athletes, only adopted to a minor degree [30]. Even in professional sports, the athletes’ performance quality is decreased after return to competition [1] and the re-injury risk remains high for years after the ACL rupture [1, 2]. Consequently, and applicable in entire populations, developing and employing strategies for secondary prevention and appropriately adapted functional diagnostics are crucial. Beyond the focus on recurrence prevention, the potential of the program in pre-operative training may be given. Pre-operative training strategies are highlighted to be of importance [31], yet, they are only carried out sparsely; therefore, a feasible intervention may be helpful.

The heterogeneity of the participants may become a limitation for the results’ interpretation and the deduction of the practical relevance of our trial. To minimize this potential bias, co-variate analyses are performed. Together with the randomized study design and the resulting respect of unknown confounders, considering the known and suggested confounders provides a sufficient statistical power. A common limitation in clinical exercise trials is the limited possibility of blinding the patients. This limitation is reduced by the superiority design (no inactive control group) of our study. To further reduce the risk of bias as much as possible, all investigators are blinded to intervention allocation.

Beyond this, the results of our study will be of importance not only for researchers and policy makers, but also for patients.

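### The only power calculation uses an unexplained 50% type II error and does not match the planned analysis, yet the Discussion calls the power sufficient

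*Protocol article*

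**What the plan says.** Under Sample size determination, the protocol article notes that no minimal clinically relevant change has been published for the Drop Jump Screening Test. It takes its scale from an earlier randomised trial: "The mean post-intervention value was 66.4% (standard deviation (SD) = 14.2"%). The target is d = 0.3, explained as "mean change of 0.3 × SD", with "a two-sided alpha-error level of 5% and beta-error level of = 50"%. From this, "data from *N* = 174 (*n* = 87 per group) participants have to be analyzed". The purpose is given as the number of "participants have to be analyzed to statistically find a between-group difference using gain-score analyses". Then: "Assuming a dropout-rate of 30%, a total of 250 (*n* = 125 per group) patients will be included".

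Under Statistical analysis, the primary outcome is analysed as confirmatory. Gains from baseline to each later time point go into a repeated-measures ANCOVA with the baseline value and several other covariates. The main statistics are run on two data structures, one time-based and one function-based. Study flow gives at least five and at most 12 measurements per participant.

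The Discussion, after describing covariate analysis as the answer to participant heterogeneity, says that, together with randomisation, "considering the known and suggested confounders provides a sufficient statistical power".

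**The concern.** A confirmatory superiority trial is normally sized so that it would probably detect its own target effect. Here the stated "beta-error level of = 50"% means that the comparison used for sizing misses the target as often as it finds it. The article does not say why this is acceptable, and it later describes the power as sufficient.

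There is also a mismatch. The calculation treats the data as one unadjusted value per patient, using the SD of post-intervention values. The planned model has a baseline covariate and repeated measurements. The only power figure in the article therefore does not describe the analysis that will be run, and the claim about that analysis has no figure behind it.

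At stake is how the primary result can be interpreted. A reader who accepts the Discussion sentence has no means of knowing how likely a true effect of 4.26 points was to be detected.

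**Working it through.** **Inputs from Sample size determination:** d = 0.3, SD 14.2 percentage points, two-sided alpha 0.05, beta 0.50, 87 per group, 30% dropout. Target in points: 0.3 × 14.2 = 4.26.

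**1. Reproducing the stated figure.** For a two-sample t-test the noncentrality is d × √(n/2) = 0.3 × √43.5 = 1.98, almost equal to the critical value of about 1.97. Power is therefore about one half: 50.3% by the noncentral t. Solving for 50% power gives n = 86.3, rounded up to 87 per group, or 174. With dropout, 87 / 0.70 = 124.3, so 125 per group and 250 in total. All the stated figures agree.

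**2. Is the 50% a misprint?** With beta 20% the same inputs need 175.4, so 176 per group (352 analysed; 352 / 0.70 = 503 enrolled). With beta 5% they need 290 per group. Only 50% gives 87.

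**3. What 87 per group can detect, unadjusted.** 80% power is reached at d = 0.427, and 0.427 × 14.2 = 6.1 points. The expected 95% confidence interval half-width is 1.96 × 14.2 × √(2/87) = 4.22 points, about the size of the target.

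**4. Planned type of analysis, one follow-up time point.** Let r be the baseline-to-follow-up correlation. The article gives none, so every r below is an assumption. The target stays at 0.3 of the post-value SD.

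Baseline-adjusted (ANCOVA): effective d = 0.3 / √(1 − r²). Unadjusted gain score: effective d = 0.3 / √(2(1 − r)).

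| r (assumed) | ANCOVA power | Unadjusted gain-score power |
|---|---|---|
| 0.3 | 54% | 38% |
| 0.4 | 57% | 44% |
| 0.5 | 62% | 50% |
| 0.6 | 69% | 59% |
| 0.7 | 79% | 72% |

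ANCOVA at one time point reaches 80% only at r of about 0.71.

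**5. Planned type of analysis, average over follow-up.** Five measurements leave four after baseline. For a baseline-adjusted mean of four values, the variance in units of SD² is Var(mean) − Cov(mean, baseline)². This assumes a constant effect and a test of the averaged group difference.

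| Correlation structure (assumed) | r = 0.3 | r = 0.5 | r = 0.7 |
|---|---|---|---|
| Equal correlation | 88.7% | 89.5% | 95.8% |
| First-order autoregressive | 89.3% | 82.6% | 80.9% |

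Example, equal correlation with r = 0.5: Var(mean) = (1 + 3 × 0.5)/4 = 0.625. Subtracting 0.5² = 0.25 leaves 0.375. Effective d = 0.3 / √0.375 = 0.49.

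**6. What could lower these figures.** If the effect appears late, or if the conclusion rests on single time points with the planned multiplicity corrections, step 5 is too favourable. As an illustration, if alpha were split to 2.5% between the two data structures (an assumption; the article does not fix this), the unadjusted power would be 39%.

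**The case against.** The strongest reply is that the Discussion sentence does not refer to the unadjusted calculation at all. It concerns covariate adjustment, the planned model includes the baseline value, and patients are measured repeatedly. Steps 4 and 5 show that such a model can have well over 50% power, and over 80% under favourable conditions. This stands. The sentence is unsupported, but it is not shown to be false.

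It follows that one tempting reading must be set aside: a reader might infer that the planned analysis itself has exactly 50% power. The article does not support that. The 50% belongs to the simple comparison used for sizing.

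A reader might also infer that a non-significant result would be taken as proof that the program does not work. No section plans such a reading. The Background only states a null hypothesis of no systematic superiority.

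It can also be said that nothing is hidden, since the 50% stands in the same sentence as the sample size, and that an article condenses a fuller plan. The first is true. The second does not help here: both the power level and the claim of sufficiency are stated in the article, and the one calculation shown does not support the claim.

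**Conclusion.** The concern holds in a limited form. The sample size arithmetic is correct, and the 50% type II error is real and unexplained. For the unadjusted comparison at one time point, power is 50.3% at 4.26 points and 80% only at 6.1 points.

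The claim of sufficient power rests on no figure in the article and conflicts with the only calculation shown. The power of the planned analysis is not established. It ranges from about 38% to about 96%, depending on which contrast is primary (gain score or ANCOVA, one time point or an average), on correlations of 0.3 to 0.7 that are assumptions here, and on whether the effect is constant over follow-up. The true figure may be adequate, but the article gives no basis for saying so.

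**What to change.** No additional patients are needed.

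1. **Sample size determination.** Label the 50% power at d = 0.3, and the 80% power at d = 0.43 (6.1 points), as figures for an unadjusted two-group comparison at one time point. Separately, name the primary ANCOVA contrast and state its power for 87 per group over a stated range of correlations. Keep the two sets of figures apart, because the unadjusted ones do not carry over to the adjusted model.
2. **Discussion.** Delete the statement that power is sufficient, or replace it with the figure computed under item 1.
3. **Interpretation.** Report the primary result with its 95% confidence interval. Do not take non-significance as evidence of no effect unless the interval excludes 4.26 points. In the unadjusted comparison this would need an estimate below about 4.26 − 4.22 = 0.04 points, so most non-significant results in favour of Stop-X would be inconclusive.

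The cost is wording and one short calculation. The drawback is that the stated power may look less favourable than the present text suggests.

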#### Recruitment and screening

Potential participants are recruited by personal addressing through one of the center heads (physicians) during or after a scheduled visit. Following application of the inclusion and exclusion criteria, patients are approved by the physician in charge.

Inclusion and exclusion criteria:

Adults (aged at surgery from 18 to 35 years) with remaining anterior knee instability after acute unilateral ACL rupture and having passed, or being scheduled for, an arthroscopically applied, anatomic single reconstruction (< 3 months between rupture and reconstruction) with autologous hamstrings tendon, will be included. Only participants engaged in sport (self-reported) prior to the injury and with the aim to return to their previous sporting activity are included. Exclusion criteria for the multimodal assessment protocol are: (1) meniscus lesion > 2 cm, (2) cartilage lesion > International Cartilage Regeneration and Joint Preservation Society (ICRS) grade II, (3) previous musculoskeletal surgery of the uninvolved (contralateral) leg, (4) leg mal-alignment > 5°, (5) multi-ligament injury pattern, (6) postoperative re-injury, (7) acute or chronic inflammation of the musculoskeletal system or muscle soreness and (8) pregnancy.

#### Randomization procedure and blinding

After sequential inclusion, volunteers are block-randomized using a non-stratified, permuted block with varying length strategy (*N* = 15 blocks; patient distribution = 1:1 in each arm/group. Each study sites’ participants are randomized using the site-specific randomization lists; the randomization sequence is generated using a computer-based algorithm (www.randomisation.com). All assessors and study personnel other than one study coordinator (DN) are blinded to group allocation. Participants are told not to communicate their group allocation to other participants or study staff. All data assessed are processed and analyzed blinded to treatment allocation.

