### Statistical analysis

Following range plausibility control based on potentially reachable physiological values, a visual control for non-plausible outliers will be performed. Afterwards, all analyses will be performed based on the underlying assumptions for parametric, or rather, non-parametric testing. In detail, for all difference testing, data and variance distribution (i.e., normality) are checked; for all correlation analyses, residuals, auto correlation, and heteroscedasticity, are checked. The alpha-error threshold is set at 5%, all *p* values below are considered significant.

The analyses for the primary outcome, DJST, are done confirmatory, alpha-error corrections (Bonferroni-Holm for paired and Sidak-Holm for unpaired analyses) are performed for multiple used samples and post-hoc analyses following significant omnibus testing, whilst the alpha-error remains unadjusted for the exploratory (secondary) analyses.

The main statistics are performed twice (two different data structures): once on a time-based and once on a functional-based data structure. All repeated measures statistics are thus first performed for the time-based data structure where statistics are performed on all outcomes assessed at the same real-time after reconstruction. Secondly, functional-based data-structure analyses are performed, where the first (baseline) measurement is the first “real” measurement at the time of being cleared for the assessment (varying times of 4–8 months post reconstruction). For each of the analyses on the two datasets, gain-score analyses are performed for differences from pre (baseline) to post (each following time point) of all outcomes using repeated-measures analyses of co-variance (rmANCOVAs) with potential confounders as co-variates (baseline values, injury history, sex, type and amount of sport, age, co-morbidities). In case of a systematic impact of confounders on statistics, z-transformed values are calculated and used for further analyses. Afterwards, survival analyses by means of Kaplan-Meier plotting plus between group-difference analyses using log-rank tests are performed. Hazard ratio estimations will be calculated. Events will be: (1) Time point of unrestricted RTS decision, (2) Time point of functional criterion RTS succeeded (> 60% normalized knee-separation distance at DJST) and (3) Time point of revision surgery, re-injury or subsequent injury.

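### Site-specific block lists are called non-stratified and site is absent from the analyses as described, so precision is forgone if outcomes differ between sites

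*Protocol article*

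**What the plan says.** The trial has several centres: "A multicenter, single-blind, randomized controlled, superiority, two-arm trial will be adopted" (Protocol article, Study design, ethics and informed consent).

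Under Randomization procedure and blinding, the article states that "volunteers are block-randomized using a non-stratified, permuted block with varying length strategy", with "patient distribution = 1:1 in each arm/group". The following sentence says of each site that its "participants are randomized using the site-specific randomization lists".

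Under Statistical analysis, the gain-score models are repeated-measures ANCOVAs with "potential confounders as co-variates (baseline values, injury history, sex, type and amount of sport, age, co-morbidities"). Site is not among these terms. For the time-to-event endpoints, "between group-difference analyses using log-rank tests are performed", and hazard ratios are to be estimated. No strata are mentioned for either.

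Under Sample size determination, the calculation is a plain two-group comparison with "a two-sided alpha-error level of 5% and beta-error level of = 50"%. It makes no allowance for site.

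**The concern.** Two things do not fit together. First, a separate permuted-block list for each site is the usual way to stratify by site, so the label contradicts the procedure described directly after it. An analyst who relies on the label would see no reason to carry site into the model.

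Second, the analysis should normally reflect the factors that the allocation controls. Blocking within site makes the arms nearly equal in size at every site, so differences between sites largely cancel out of the treatment contrast. A model without site does not take credit for this: it leaves the between-site variation in the residual, and the estimated standard error is then larger than the true one. At stake are precision and the nominal level of the test, in a trial planned with no reserve of power.

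**Working it through.** **Inputs from the documents.** Effect d = 0.3, two-sided alpha 5%, beta 50%, 87 analysed per arm, 30% dropout, 250 enrolled (Sample size determination).

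**Input not in the documents.** The share of outcome variance that lies between sites (ICC, ρ). It is assumed here to range from 0 to 0.10, and is read as the share left after the listed covariates. The number and size of the sites are not given either.

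**Step 1: the plan's own figure.** The exact two-sample t-test (noncentral t) at d = 0.3 has power 0.4985 with 86 per arm and 0.5031 with 87. So 87 per arm, 174 in all, reproduces. For dropout, 87 / 0.70 = 124.3, rounded up to 125 per arm, gives 250. The normal approximation used below gives 50.7% at 87 per arm.

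**Step 2: formulas.** Set the total variance to 1 and assume balance within sites.
- Variance of the contrast assumed by a model without site: 2/87. True variance: (1 − ρ) × 2/87.
- Overstatement of the standard error: 1/√(1 − ρ).
- True type I error without site: 2 × [1 − Φ(1.96/√(1 − ρ))].
- Expected test statistic without site: m = 0.3/√(2/87) = 1.979.
- Power without site: 1 − Φ((1.96 − m)/√(1 − ρ)).
- Power with site: Φ(m/√(1 − ρ) − 1.96).

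Example at ρ = 0.05: √0.95 = 0.9747. Then 1.96/0.9747 = 2.011, so the type I error is 4.4%. And 1.979/0.9747 − 1.96 = 0.070, so power with site is 52.8%.

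**Step 3: results.**

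| Assumed ρ | SE overstated by | Type I error, site omitted | Power, site omitted | Power, site in model | Gain forgone (points) |
|---|---|---|---|---|---|
| 0 | 0% | 5.0% | 50.7% | 50.7% | 0 |
| 0.01 | 0.5% | 4.9% | 50.7% | 51.1% | 0.4 |
| 0.02 | 1.0% | 4.8% | 50.7% | 51.5% | 0.8 |
| 0.05 | 2.6% | 4.4% | 50.8% | 52.8% | 2.0 |
| 0.10 | 5.4% | 3.9% | 50.8% | 55.0% | 4.2 |

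**Step 4: check by simulation.** The closed formulas assume perfect balance within sites. A simulation dropped that assumption: 174 patients, 3, 5 or 10 equal sites, site-specific blocks of 4/6/8 or of 16, and 4,000 runs per setting. Adding site raised power by 1.3 to 1.9 points at ρ = 0.05 and by 2.1 to 4.0 points at ρ = 0.10. At ρ = 0 the two models differed by at most 0.5 points. The direction agrees, and the gains are somewhat smaller than the formula gives.

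No size was computed for the log-rank or hazard-ratio analyses. The same reasoning gives the direction only.

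**The case against.** The strongest case against the point has four parts.

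- **The site effect on the primary outcome may be small.** The drop-jump test is self-administered, filmed on the participant's own phone and rated blind from video, so no site assessor takes the measurement. Eligibility is narrow, and baseline is a covariate in a gain-score analysis, which removes much of any stable difference in level between sites. This stands, and it is why the range above starts at 0. At ρ = 0.20 the formulas would give a type I error of 2.8% and power of 60.0% with site, but nothing in the documents supports a value that high.
- **No planned power is lost.** A reader might infer that omitting site pushes the trial below its target or makes the test invalid. It does neither: power without site stays at 50.7% to 50.8% across the table, and the type I error lies at or below 5%.
- **The article is condensed.** A reader might infer that site is left out of every analysis. The article cannot show that. An analysis plan that is not shown may add site, and silence on log-rank strata is weak evidence. For the ANCOVA, however, the covariate list is printed without any sign that it is only illustrative, so adding site later would depart from it.
- **The label may mean only that no patient characteristic is used.** That is a possible reading, and allocation itself is unaffected. The wording still misdescribes the design.

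A reader might also infer that time to the return-to-sport decision is affected most, because release for training and the return decision involve local clinicians. The article describes these as shared, criteria-based decisions that also involve the athlete, and it gives no figure for variation between sites. That ranking is unsupported.

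**Conclusion.** The point holds in a limited form. The wording conflict is certain from the text. Site is absent from the printed ANCOVA covariates and is not mentioned for the time-to-event analyses.

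The statistical consequence is conditional on outcomes differing between sites. It is nil without a site effect, about 2 points of power or less for an ICC up to 5%, and about 4 points at 10%, with a mildly conservative test. These figures rest on an assumed ICC, near balance within sites and a normal approximation. There is no bias, no added false-positive risk and no fall below planned power. The planned power of 50% is a separate and much larger matter, since the same inputs need 176 per arm for 80%. The present point is worth acting on because the correction is nearly free.

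**What to change.** 1. Describe the randomisation as permuted-block, stratified by site and by no patient characteristic.
2. Add site as a factor to the drop-jump and secondary-outcome models. Fix a rule for pooling very small sites before unblinding.
3. Stratify the log-rank tests and the hazard-ratio estimates by site, using the same pooling rule.

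The cost is a change of wording, one model term (one degree of freedom per site beyond the first) and a short pooling rule. No extra patients, visits or data are needed, because site is already known for every participant.
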